## Discussion

The MS community is looking for interventions to help alleviate the disabling sequelae of MS. Exercise is a well-known intervention which has known benefits to all, it has no negative side effects when prescribed appropriately, it has other benefits beyond disability such as reducing obesity and cardiovascular risk. It is hypothesized to have neurorehabiliative effects [15] and it is an intervention that is accessible to all at little cost. Yet, few exercise regularly. For people with MS, our survey of exercise barriers [44] showed that a major barrier was in not knowing what to do, being afraid of heat exhaustion, and fatigue. Proper instruction and tailoring exercise to specific needs could overcome these barriers.

The exercise program is novel. It incorporates all elements of the “Activity Pyramid” [92]: lifestyle activity; aerobic activity, strength and flexibility. It incorporates the notion of a “push-day” when persons are encouraged to push themselves to exercise intensely for short bursts. It is designed to add some form of exercise to most days.

In addition, this trial incorporates a number of statistical approaches rarely applied in the rehabilitation field, yet this field typically conducts research that would benefit from more modern statistical and methodological approaches.

The primary outcome is binary not a difference of two means. This is a more interpretable outcome and facilitates knowledge translation as people with MS and their care providers can readily understand what proportion of people made a relevant gain, whereas a mean difference may not apply to individual subjects. This outcome permits a calculation of number-needed-to-treat (NNT) [93], a very useful statistic in terms on comparative effectiveness [94]. With this outcome, it is also possible for research results to present data showing factors increasing the probability of a positive response permitting participants and providers alike to identify whether an individual is in a group more or less likely to benefit and perhaps provide additional interventions to increase probability of response.

All secondary outcomes will be analysed using a global response statistic. A challenge with trials of complex interventions particularly those which tailor the intervention to patient needs, which typify rehabilitation-type interventions, is that no one outcome is likely to capture the effect equally for each person and analysing each outcome separately is often considered suspect in some research cultures. Recently in a 2009 publication in the Archives of Physical Medicine and Rehabilitation, Bagiella [85] demonstrates the value of using modern statistical methods to combine multiple outcomes into a composite response variable. We have demonstrated the benefit of this approach in evaluating a case-management intervention for people discharged home post-stroke [95].

We will also use propensity scoring, a widely used epidemiologic method to improve validity and precision when there is a need to consider multiple confounders that also may be correlated; a propensity score is calculated for each person based on their probability of taking an action or treatment, here engaging in exercise. Using this method, the propensity score is the adjustment variable, either as a continuous variable or a categorical variable such as quintiles (depending on linearity). The advantage is that multiple confounders can be combined in a single propensity score; adjustment in the analysis for the single propensity score also adjusts for all the confounders summarized in the score [89].

The results of the trial will contribute needed evidence for the development of guidelines for exercise for MS. If proven effective, the content will be made available at no cost.

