### Primary outcome

The first primary effectiveness outcome will be VO_2peak_ using a modified Bruce protocol on the cycle ergometer. Briefly, peak oxygen consumption (VO_2peak_) will be determined using an incremental graded cycle ergometer test. The person will properly seated and the bicycle adjusted for optimally positioning. Rate of Perceived Exertion (RPE), heart rate, and blood pressure will be taken at each workload, in addition to assessing oxygen consumption and CO_2_ production. The person will cycle for 3 minutes at 0 watts, 10 watts and 20 watts (9 minutes) and subsequently, at intervals of 1 minute, the work load will be increased by 10 watts. People will be considered to have reached their peak exertion if one of the following criteria are met [80]: (i) reached their age-predicted heart rate of 220-age; (ii) a rating of perceived exertion of at least 17 on the Borg scale; (iii) a respiratory rate of 35 breaths per minute; (iv) pedalling rate of 50 to 80 repetitions per minute cannot be maintained; or (v) the person says they can do no more. Our effectiveness indicator is the proportion of people making a 10% change in VO_2peak_ at the end of the 12 month intervention.

In addition, each person will also complete, the Modified Canadian Aerobic Fitness Test (mCAFT) [81], which is a graded step test and can predict VO_2peak_ using the regression equation we have recently published [46]. This test will be completed only at interim evaluations (3, 6, and 18 months) or if the person misses one of the VO_2peak_ assessments.

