### Sample size

Sample size is based on a test of proportions. Assuming a range of response proportions in the General Guideline Group of 0.2 to 0.5, we have powered this study at 80% to detect a relative risk of >1.5 in favour of the MSTEP Group (Type I error 0.05). A sample size of 120 per group (total sample size of 240) is targeted.

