### Statistical methods

The main analysis will be logistic regression to test the main hypothesis related to the superiority of the MSTEP program based on a greater proportion of people making a clinically relevant gain in exercise capacity at 1 year. A secondary outcome will be the differences in proportions at 2 years also using logistic regression. The analysis will be based on intention-to-treat and all persons will be analysed in the groups to which they were randomized.

A secondary analysis will estimate the impact of exercise on the other relevant outcomes. For this approach, each outcome will be converted to a binary response variable based on published clinically meaningful changes (see Table 1) and generalized estimating equations (GEE) will be used to test the rate of response in the MSTEP program to the rate of response in the general guideline approach [85,86]. If there is a statistically significant effect of the intervention, then and only then, can the effects of the separate outcomes be interpreted as real [86].

The role of exercise engagement in explaining outcome variation will be estimated using multivariate modeling for both logistic and longitudinal growth models. A separate analysis will be conducted to examine relapse rate and other adverse events. All of these analyses will be adjusted for confounders using propensity scoring [27,87-89]. Factors used in the propensity score are: extent of complaints (co-ordination, weakness or heaviness in legs, anxiety/depression, bladder problems), presence of children, and exercise enjoyment at study entry [44]. Adjustment will also include age and sex and additional prognostic variables which improve model fit.

If people are unable to do the VO_2_peak test or the data from this test is aberrant (person did not reach a peak), we will use a validated a regression equation to estimate VO_2_peak measured in ml/kg/min from submaximal tests [46]. The equation, which is based on our pilot work on 60 subjects, is: VO_2peak_ = -11.83 + 1.78(Men) + 0. 2*each 10 meters distance walked in 6 minutes + 16.3 * L/min oxygen consumption estimated from the completed stage of step test.

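### The stated 80% power for a relative risk of 1.5 holds only for control response rates of about 0.36 or more, and the article names no supportive between-arm analysis of measured VO2peak

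*Protocol article*

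**What the plan says.** The Sample size section says "Sample size is based on a test of proportions". It assumes response proportions of 0.2 to 0.5 in the general guideline group and states that "we have powered this study at 80% to detect a relative risk of >1.5 in favour of the MSTEP Group", with type I error 0.05 and 120 per group (240 in all). It does not state whether the test is one- or two-sided and gives no allowance for loss.

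On the analysis, the Statistical methods section says "The main analysis will be logistic regression to test the main hypothesis related to the superiority of the MSTEP program", based on the proportion with a clinically relevant gain at 1 year. The same approach is used later: "A secondary outcome will be the differences in proportions at 2 years also using logistic regression". For the remaining outcomes, "each outcome will be converted to a binary response variable based on published clinically meaningful changes", and these are tested by GEE. The Discussion confirms the position for the primary outcome ("The primary outcome is binary not a difference of two means") and gives reasons: interpretability, number needed to treat, and the limited meaning of a mean difference for an individual.

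The one named model that may use measured values is in the Statistical methods section: "The role of exercise engagement in explaining outcome variation will be estimated using multivariate modeling for both logistic and longitudinal growth models". That sentence gives the growth models an explanatory purpose. It does not describe a randomized comparison of VO2peak.

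**The concern.** The power claim covers a whole range of control rates with one sample size and one relative risk. For a fixed relative risk, the absolute difference shrinks as the control rate falls: 1.5 means 0.50 against 0.75 at the top of the range but only 0.20 against 0.30 at the bottom. One sample size is therefore unlikely to give the same power throughout, and the low end is where a shortfall would appear.

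The second part follows from the first. VO2peak is a continuous measurement, yet each between-arm test of it that the article describes uses only which side of a 10% cut a participant falls on. If the control rate is low and the responder test is not significant, readers will want to know how far exercise capacity moved on average and how precisely that is known. The article names no such estimate, and one chosen after unblinding would look data-driven.

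**Working it through.** **Inputs.** From the Sample size section: control rate p0 from 0.2 to 0.5, relative risk 1.5 (so p1 = 1.5 × p0), n = 120 per arm, alpha 0.05. From Trial design: 1:1 allocation. Assumed: two-sided test and no loss to follow-up.

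**Step 1, the plan's own figure.** Pooled-variance test of two proportions, with p̄ = (p0 + p1)/2:

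Power = Φ{ [(p1 − p0)√n − 1.96√(2p̄(1 − p̄))] / √(p0(1 − p0) + p1(1 − p1)) }

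- p0 = 0.20, p1 = 0.30, p̄ = 0.25: (0.10 × 10.954 − 1.96 × 0.612)/0.608 = −0.17, so power is 43%.
- p0 = 0.30, p1 = 0.45, p̄ = 0.375: (0.15 × 10.954 − 1.96 × 0.685)/0.676 = 0.45, so power is 67%.
- p0 = 0.36, p1 = 0.54, p̄ = 0.45: (0.18 × 10.954 − 1.96 × 0.704)/0.692 = 0.86, so power is 80%.

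| Control rate | Power at RR 1.5, n = 120 | n per arm for 80% | RR detectable with 80% |
|---|---|---|---|
| 0.20 | 43% | 294 | 1.81 |
| 0.25 | 55% | 215 | 1.68 |
| 0.30 | 67% | 163 | 1.59 |
| 0.35 | 78% | 125 | 1.51 |
| 0.36 | 80% | 119 | – |
| 0.40 | 88% | 97 | 1.45 |
| 0.50 | 98% | 58 | 1.35 |

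The stated 120 per group is reproduced at a control rate of about 0.36, but not below it.

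**Step 2, other ways of doing the calculation.** A one-sided 5% test gives 56% at 0.20, 67% at 0.25 and 78% at 0.30. A Wald test on the log odds ratio gives 43% at 0.20 and 67% at 0.30; on the log relative risk, 42% and 65%. A continuity correction raises the n needed at 0.20 from 294 to 313. None of these rescues the lower part of the range.

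**Step 3, loss to follow-up (assumed, complete cases).** With 0%, 15% and 20% loss (120, 102 and 96 per arm), power is 43%, 38% and 36% at control 0.20, and 67%, 60% and 57% at 0.30.

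**Step 4, what the measured value could add.** Assume that change in VO2peak is normal with equal SD in both arms. The shift that produces RR 1.5 is d = z(p1) − z(p0) in SD units, and power = Φ(d√(n/2) − 1.96), with √60 = 7.746.

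- Control 0.20: d = −0.524 + 0.842 = 0.317; 0.317 × 7.746 − 1.96 = 0.50; power 69%, against 43% for the responder test.
- Control 0.30: d = 0.399; 0.399 × 7.746 − 1.96 = 1.13; power 87%, against 67%.

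These figures do not count baseline adjustment.

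**Step 5, dependence on equal SD.** Let the SD of change be 1.2 times larger in the MSTEP arm, with control 0.20 and MSTEP 0.30. The cut lies at 0.842 control SDs, so the MSTEP mean is 0.842 − 1.2 × 0.524 = 0.212. The standard error is √((1 + 1.44)/120) = 0.143, and power is Φ(0.212/0.143 − 1.96), about 32%. That is below the 43% of the responder test.

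**The case against.** The strongest objection is that this is a condensed article. A supportive model is the kind of detail commonly left to a full protocol or SAP, and neither is shown. That stands as a limit: a reader might infer that the trial has no analysis of measured VO2peak anywhere, and the article cannot support that. It supports only a statement about the analyses it describes. The supportive model is therefore a recommendation for a cheap gain; the error is the power sentence, which is wrong whatever an SAP contains.

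The authors could also say that a relative risk written as above 1.5 includes larger effects. The sentence still gives 1.5 as the threshold, and at 0.20 the detectable value is 1.81.

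Four stronger readings are tempting and do not hold:

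- *The binary primary is a mistake.* It is a reasoned choice, and the Discussion's arguments for it are sound as far as they go.
- *The trial will probably miss a relative risk of 1.5 at any control rate from 0.2 to 0.35.* Power passes 50% at a control rate of about 0.23 with full follow-up and is 78% at 0.35. A miss is the likelier outcome only below about 0.23.
- *A null responder result would be uninformative.* Logistic regression still yields an odds ratio with a confidence interval. It would be imprecise at low control rates, but not empty.
- *Analysing the measured value repairs the power.* Even under favourable assumptions it reaches about 69% at 0.20. The Discussion itself argues that a tailored programme will not affect everyone equally, and this makes equal SD doubtful.

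**Conclusion.** The power statement is wrong as written for control rates below about 0.36. That is roughly the lower half of the stated range: (0.36 − 0.20)/(0.50 − 0.20) = 0.53. The gap is largest at 0.20, where power is about 43% instead of 80%. The result rests on a two-sided 5% test at exactly RR 1.5 with no loss; with a one-sided test the limit moves only to about 0.31.

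Separately, the article describes between-arm tests of VO2peak only as a responder proportion. A single supportive estimate of the measured value would be worth adding as an aid to interpretation. Its power advantage is conditional on a normal change with similar SD in both arms, and it should not be presented as a remedy for the shortfall.

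**What to change.** 1. **Restate the power sentence; leave the sample size as it is.** Either claim 80% power for RR 1.5 only for control rates of about 0.36 or more, or give the relative risk detectable with 80% power at each rate: 1.81 at 0.20, 1.59 at 0.30, 1.45 at 0.40 and 1.35 at 0.50. State that the test is two-sided and that no loss is counted. The cost is one sentence or a small table.

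2. **Keep the 10% responder proportion as primary and pre-specify one supportive model.** Fit an ANCOVA of log VO2peak at 12 months, and again at 24, on log entry VO2peak, arm, site and Fampyra stratum (the two factors in the Randomization section), using the multiple imputation already planned. Report the arm effect as a percent difference with its 95% confidence interval, beside the responder result and with no superiority claim resting on it. The log scale fits a threshold that is itself a percentage change.

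The model uses data already collected. The downsides are modest: the two results may differ and would then need comment, and VO2peak values predicted from the regression equation in the Statistical methods section would enter the model with their prediction error.
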